## 10. ELIGIBILITY CRITERIA

### Inclusion criteria

1. Age range 18–64 years
2. None of the patients' complaints have been present before March 2020
3. Verified positive COVID-19 PCR test (for the post-COVID-19 group only)
4. Symptoms have persisted for at least 3 months after COVID-19 infection

5. Reported worsening of symptoms after exertion
6. No previous history of cardiovascular disease
7. No history of generalized anxiety disorder or somatic symptom disorder
8. Written informed consent

### **Exclusion criteria**

1. Age outside the range of 18–64 years
2. Patient's symptoms occurred before March 2020
3. No verified positive COVID-19 PCR test
4. Symptoms disappeared within 3 months of COVID-19 infection
5. Has not reported worsening of symptoms after exertion
6. Current or previous cardiovascular disease
7. Current or history of generalized anxiety disorder or somatic symptom disorder

## **11. INTERVENTIONS**

### **11a. Description of interventions for each group**

#### Exercise response

Subjects will perform high-intensity-interval training (HIIT), moderate intensity continuous exercise (MICT) and strength training (ST). The acute exercise responses will be closely monitored, including measurements of O2 saturation, heart rate, blood pressure, rating of perceived exertion (Borg scale 6–20) and blood lactate. In addition, symptoms via multiple validated questionnaires and blood samples will be collected before, immediately after each exercise session to describe leukocyte and cytokine release. After a 48-hour rest period subjects will return to the laboratory for symptom assessment, submaximal exercise response (CPET), and blood sampling.

#### Physiological assessment (characterization)

Subjects will perform a series of baseline assessment including neurophysiological function, circulatory and vascular function, blood volume assessment, respiratory/ventilatory function, maximal oxygen uptake, strength, physical function and fitness, blood status and muscle biopsy.

#### 1 year follow-up

Subjects will perform the same series of baseline assessment in 1-year time, including neurophysiological function, circulatory and vascular function, blood volume assessment, respiratory/ventilatory function, maximal oxygen uptake, strength, physical function and fitness, blood status and muscle biopsy.

## 11b. Criteria for discontinuation or modification of interventions

All subjects will be informed verbally and in writing (consent form) that they have the right to discontinue the study at any time, without this affecting their standard medical care.

Researchers will be in contact with participants during their participation to ensure that their condition has not worsened due to or during the study participation. The research team will meet on a weekly basis and discuss such matters with the responsible physician.

## 12. EXPLANATIONS OF THE ASSESSEMETNS – OUTCOMES

### Exercise trials (HIIT, MICT, ST)

Subjects will perform 5 minutes warm-up, then either of the following exercise training protocols in a randomized order, followed by 5 minutes of active recovery. **MICT:** Continuous 30 min cycling at moderate intensity **HIIT:** 5 x 1 min cycling at high intensity, 1 min rest **ST:** 3 sets x 10 repetitions of 3 exercises covering large muscle groups of the lower and upper body (2 min recovery between sets). Exercise sessions will be thoroughly and continuously monitored, including measurements of O2 saturation, blood pressure, and blood lactate. In addition, blood samples will be collected before, immediately after, 1h and 48h post each exercise session to describe leukocyte and cytokine release. At 48 hours follow up, post-exercise symptoms and exercise responses to a monitored graded exhaustion test will also be reported.

**HIIT session:** 5 x 1-min intervals on a cycle ergometer (Monark LC6, Vansbro, Sweden) with a workload equal to 90% of the workload the patients achieve during the initial cardiopulmonary exercise testing (CPET) at baseline. Each interval will be interrupted by a 1-minute rest period in a seated position. Intensity is increased to be  $\geq 16$  on the Borg scale at the end of the session. The workload is increased if the perceived exertion is lower and decreased if subjects are unable to achieve an RPM above 55.

**MICT session:** 30 minutes of continuous cycling (Monark LC6, Vansbro, Sweden). Participants will be asked to cycle at 50% of the workload achieved during the baseline CPET. The intensity aims to correspond to 12–14 according to the Borg scale. If the rating is lower, the workload is increased and vice versa if the rating is higher. The monitoring of RPE is done every five minutes during the training session.

**ST session:** This session consists of 3 different exercises designed to train the entire body in the following order a) deadlifts, b) push-ups and c) knee-extensions. All three exercises will be conducted in three sets, with three minutes of rest between each set and/or exercises. The session will begin with three sets of 10 repetitions of deadlifts on a flywheel device (Kinetic Box (Kbox), Exxentric AB TM, Bromma, Sweden), equipped with one 4.6-kg flywheel with a moment of inertia of 0.07 kg·m^-2. Participants will be instructed verbally and visually by the researcher and will familiarize themselves with six repetitions as a warm-up before starting the exercise sets. Participants will be asked to pull as hard as they can during the sets and will be verbally encouraged by the researcher. The second exercise will be

push-ups, performed in three sets. The goal for the push-ups will be to complete 10–15 repetitions in each set. Participants can choose to perform the push-up as a normal push-up (feet and arms on the floor), a push-up with knees on the floor, or with knees on the floor and arms raised 25 cm. They will also be instructed to leave one repetition in reserve to get reasonably close in repetitions in the following sets. Finally, the participants will perform three sets of 10 repetitions of knee extensions on a flywheel knee extension machine (YoYo Technology Inc., Stockholm, Sweden) equipped with an inertia that, according to the manufacturer's instructions, corresponds to  $0.054 \text{ kg}\cdot\text{m}^{-2}$ . Participants will sit and perform the exercise from  $\sim 80^\circ$  knee joint angle to  $\sim 175^\circ$  with full engagement throughout the sets, with encouragement from research staff. All three exercises will have three minutes of rest between sets to ensure adequate rest, and blood pressure (BP), heart rate (HR), oxygen saturation ( $\text{SaO}_2$ ), and Borg scale ratings will be monitored after each exercise.

### COVID-19-related symptoms and post-exertional symptoms

Post-exertional symptoms and general health of subjects will be captured through validated questionnaires at baseline and 1-year follow up (SF-36, mMRC dyspnea scale, DSQ-PEM).

In addition, subjects will report PEM symptoms before, immediately and 48h following acute exercise sessions using the following tools: VAS 0–10 for 10 symptoms (fatigue, muscle pain, joint pain, lymph nodes, concentration, memory, headache, fever, sore throat), Multifactorial Fatigue Inventory (MFI), Profile of Mood States (POMS). Finally, Somatic and Psychological Health REport (SPHERE) will be administered before and 48h after exercise trials.

### Physical function and muscle strength and accelerometers

Physical function will be assessed via the validated 6-minute walk test. Handgrip strength will be measured via a hand dynamometer (maximal voluntary contraction), whereas isometric and dynamic knee extensor muscle function through isokinetic dynamometry (Biodex). Accelerometers will be given to participants to assess physical activity.

The 6-minute walk test: Subjects will be asked to walk for 6 minutes as fast as they can in a pre-determined area of 30 meters length according to standard American Thoracic Society guidelines. Distance in meters will be used to assess their physical fitness.

Handgrip strength: The gold standard Jama hydraulic hand dynamometer (Model 5030 J1, Sammons Preston Rolyan, Bolingbrook, IL, USA) will be used to measure handgrip strength. Subjects will be instructed to hold the dynamometer in the dominant hand, extend the legs and arm, and hold the wrist in a neutral position, then squeeze the dynamometer as hard as possible for 4–5 seconds. The participants will have three attempts with a 1.5-minute rest in between, and the peak value from the test will be scored as the maximum grip strength.

Biodex: Maximal isometric and isokinetic strength ( $60^\circ/\text{s}$  and  $210^\circ/\text{s}$ ) will be measured using isokinetic dynamometry with a sampling frequency of 2000 Hz

(Biodex System 4 Pro, Biodex Medical Systems, NY). The chest, hip and thigh will be stabilized to the dynamometer using straps, and the ankle will be strapped to the lever arm, which will be aligned with the axis of rotation of the knee joint. The subjects will be allowed 2 attempts at each velocity (30 s rest) and the best result will be accepted as peak torque. Maximal isometric torque will be measured at knee angle 120° (60° from full extension).

**Accelerometers:** Physical activity will be assessed by accelerometers (GT3X Actigraph, USA). Participants will be asked to wear accelerometers for 7 days during the waking hours. Raw data are integrated into 60s epochs using ActiLife software and expressed as counts per minutes (cpm). Wear time will be estimated using the algorithm described Choi et al. 2011. Patients with an estimated wear time of <4 days, <10h/day will be eliminated from further analysis.

### Cardiovascular/circulatory/respiratory function and work capacity

Echocardiography, head-up TILT test and spirometry will be assessed according to established clinical procedures. Cardiopulmonary exercise test (CPET) to assess  $VO_{2peak}$  will be determined with an incremental cycling test to volitional fatigue on an electronically braked cycle ergometer using an online gas collection system. Arterial stiffness will also be captured through arteriography. Blood volume will be assessed using the CO-rebreathing method.

**Echocardiography:** A licensed biomedical scientist will conduct the echocardiographic examination using the Vivid E9 ultrasound system by General Electric in Horten, Norway with a 4V2c phased-array transducer. The subjects were positioned in the left lateral recumbent posture following a 5-minute supine rest, adhering to the clinical protocol derived from guidelines by the American Society of Echocardiography and the European Association of Cardiovascular Imaging. Subsequently, another blinded observer will quantify cardiac chamber dimensions and volumes, as well as the assessment of left ventricular systolic and diastolic function.

**Head-up TILT test (HUTT):** The examination will be performed according to clinical guidelines. Prior to the test session, participants will be instructed to abstain from medications that can alter heart rate and blood pressure for 48h, as well as alcohol for 24h. They will be also instructed not to consume large meals 2–3 hours prior to the examination, including coffee consumption. The test entailed continuous HR registration using a 5-lead electrocardiogram (cable by Advantage Medical Cables, Inc) and continuous blood pressure registration using a finger-cuff that is been calibrated according to blood pressure measured using a brachial-cuff. The hemodynamic monitoring system will be used was Finapres NOVA® (Finapres Medical Systems, Amsterdam, Netherlands). Examination will be commenced with 10-min in supine position in order to obtain baseline measurements. Following this, the HUTT is applied at 70° for 20-min, to simulate standing conditions. The analysis of hemodynamic data will be performed using NOVA Scope clinical software according to the most recent practical guidelines (2019) set forth by previous studies. The analysis will be involved a three-step process: a) data preprocessing and filtering, b) feature extraction and c) determining clinical outcomes. The primary hemodynamic parameters to be used for analysis will be the beat-to-beat systolic blood pressure (SBP), diastolic blood pressure (DPB) and

heart rate (HR). Data preprocessing and filtering includes standing time determination and extraction, data quality assessment and rejection of artifacts such as motion artifacts, calibration artifacts or misidentification of beats. Feature extraction begins with baseline values, extracted as the mean of values acquired 60–30s before standing. Peak values will be extracted within the first 10-mins of tilt, as an average of 30s. The final step of the analysis process will include determining clinical classification, according to the recent consensus statement of the European Federation of Autonomic Societies. The classifications will include normal orthostatic reaction, POTS, Syncope and orthostatic hypotension. POTS is characterized by development of symptoms with a sustained heart rate increase of  $\geq 30$  bpm or  $\geq 120$  bpm within 10 minutes of standing, with no significant blood pressure difference, i.e., SBP decreased by  $\geq 20$ mmHg and DBP  $\geq 10$ mmHg. For this study, borderline POTS is characterized by development of symptoms with a sustained heart rate increase of  $\geq 27$ -29 bpm within 10 minutes of standing, with no significant blood pressure difference, i.e., SBP decreased by  $\geq 20$ mmHg and DBP  $\geq 10$ mmHg. Syncope is characterized by a significant fall of HR or BP with loss of consciousness or inability to maintain posture. And finally, orthostatic hypotension is characterized by any HR increase with SBP decrease of  $\geq 20$ mmHG or DBP decrease of  $\geq 10$ mmHG.

**Spirometry:** The procedure will be performed by a biomedical analyst using Jaeger MasterScreen PFT powered by SentrySuite, Hoechberg, Germany, according to hospital clinical guidelines following an established protocol. Participants will be seated comfortably, with a nose clip in place to ensure that breathing occurs exclusively through the mouth. The procedure will begin with a maximal inhalation, followed by a forceful and sustained exhalation into the spirometer. Participants will be encouraged to exhale with maximal effort until their lungs are completely emptied. Multiple trials may be conducted to ensure the accuracy and consistency of the results. The spirometry variables will be the forced vital capacity (FVC), forced expiratory volume in the first second (FEV1), FEV% (FEV1/ VC MAX), maximum vital capacity (VC MAX), total lung capacity (TLC), and diffusing capacity of the lungs for carbon monoxide single breath corrected for Hb (DLCOc SB).

**Cardiopulmonary exercise testing (CPET):** A CPET will be performed to assess cardiorespiratory fitness, monitoring with an ECG to rule out potential risks of the exercise sessions in the study and subsequent CPETs. The CPET will be conducted on an RE990 electronically braked cycle ergometer (Rodby Innovation AB, Hagby, Sweden) with an online gas collection system (Jaeger®, Vyntus CPX, CareFusion, Hoechberg, Germany) to analyze exhaled gases using the breath-by-breath technique, wearing a Hans Rudolph mask. The test will begin with a three-minute rest period during which heart rate (HR), blood saturation (SaO2), blood pressure (BP), and blood lactate accumulation (bLa) will be determined. After resting, participants will begin cycling for 3 minutes without resistance at a cadence of 60 revolutions per minute (rpm). After 3 minutes, resistance will be increased to 20 watts and then gradually increased by 10, 15, 20, or 25 watts per minute, with the goal of reaching maximal effort and VO2peak in 8–12 minutes after voluntary fatigue. Throughout the test, HR will be monitored by continuous 12-lead ECG recording, BP, and perceived exertion will be recorded every other minute of the test, and bLa concentration will be measured pre and 3 minutes after the test in a capillary sample from the earlobe using a Lactate Scout+ (SensLab GmbH, Leipzig,

Germany). The test will be considered maximal ( $\text{VO}_{2\text{peak}}$ ) when two or more of the following criteria are reached: 90% of age-predicted HR ( $220 - \text{age}$ ), a respiratory exchange ratio (RER)  $\geq 1.1$ , a peak  $\text{bLa}$  of  $\geq 6 \text{ mmol}\cdot\text{l}^{-1}$ , or a perceived exertion  $\geq 18$ .  $\text{VO}_{2\text{peak}}$  will be determined as the highest 20-second average. Subjects will be verbally encouraged during the test to increase their motivation for maximal exertion.

**Arteriography:** Measurements of aortic pulse wave velocity ( $\text{PWV}_{\text{ao}}$ ) will be performed using non-invasive technique (Arteriograph, TensioMed Ltd., Budapest, Hungary). Participants will be rested in supine position for at least 10 minutes, and then a single upper arm cuff will be placed to measure  $\text{PWV}_{\text{ao}}$ . The device first measures the brachial blood pressure and then inflates the cuff to suprasystolic pressure to occlude the brachial artery. During this period, the cuff collects pure pressure signals and detects direct and reflected systolic wave peaks. The time difference between the early and late systolic peaks is equal to the time of the aortic pulse wave traveling down to the aortic bifurcation and back towards the heart. The aortic root-bifurcation transit time can be calculated, and by estimate the straight distance between the suprasternal notch and pubic bone (an acceptable estimate of the aortic length), the  $\text{PWV}_{\text{ao}}$  will be calculated by the software.

**Blood volume:** The optimized carbon monoxide rebreathing method will be used to determine tHb, from which BV and PV later were calculated using hemoglobin concentration [Hb] and hematocrit (Hct). Subjects will rest for 15 minutes before a venous blood sample will be taken from the median cubital vein. The sample will be immediately analyzed for baseline carboxyhemoglobin (%HbCO), [Hb] and Hct. End-tidal carbon monoxide (CO) will be measured at baseline and after rebreathing using a CO gas analyzer (Dräger, PAC 700, Lübeck, Germany and Honeywell, BW Solo, Charlotte, NC, USA). Throughout rebreathing, the same gas analyzer will be used to check for CO leaks. Subjects will breathe a gas mixture of chemically pure (99.97%) CO ( $0.8 \text{ mL} \times \text{kg}^{-1}$ ) and medical oxygen (AGA, Stockholm, Sweden) for 2 minutes before disconnecting from the spirometer (Blood tec GmbH, Bayreuth, Germany). Two venous blood samples (1 mL) will be taken, one before rebreathing and one 7 minutes after administration of CO. The samples will be then analyzed in duplicate for %HbCO (ABL 90 Flex, Radiometer A/S, Copenhagen, Denmark), tHb will be calculated as previously described.

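### The tilt-test rules for POTS and orthostatic hypotension overlap on either reading, and the plan gives no order for assigning one class

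*Combined protocol and SAP*

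**What the plan says.** All the wording is in the protocol, Section 12, under the head-up tilt test.

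- **Class list.** "The classifications will include normal orthostatic reaction, POTS, Syncope and orthostatic hypotension". Borderline POTS is not listed, although it is defined a few lines later. No order of precedence is stated.
- **POTS.** "POTS is characterized by development of symptoms with a sustained heart rate increase of" at least 30 bpm or at least 120 bpm within 10 minutes, "with no significant blood pressure difference, i.e., SBP decreased by" at least 20 mmHg **and** DBP by at least 10 mmHg.
- **Borderline POTS.** "borderline POTS is characterized by development of symptoms with a sustained heart rate increase of" ≥27-29 bpm, with the same pressure clause.
- **Orthostatic hypotension.** "orthostatic hypotension is characterized by any HR increase with SBP decrease of" at least 20 "mmHG or DBP decrease of" at least 10 mmHg.
- **Extracted features.** "Feature extraction begins with baseline values, extracted as the mean of values acquired" from 60 to 30 seconds before standing. For the tilt phase: "Peak values will be extracted within the first 10-mins of tilt, as an average of 30s". No other tilt-phase feature is described, and *sustained* is given no duration.

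Section 7b names the tilt test as the assessment of dysautonomia and repeats the baseline investigations at one year. Section 20 compares categorical characterization variables between patients and controls by chi-square.

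**The concern.** A classification compared between groups should put each participant in one class by a rule that two assessors would apply in the same way. Here the POTS and hypotension clauses share thresholds but use different connectors. The phrase introducing the POTS thresholds can also be read in two opposite ways: as describing what *no significant difference* means, or as describing the significant difference that must be absent.

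At stake are the counts of POTS, borderline POTS and orthostatic hypotension in both groups, at baseline and at one year. Section 6a lists orthostatic intolerance and dysautonomia among the candidate mechanisms of exercise intolerance and itself notes that the clinical definition of POTS has become diluted, so these counts are likely to be read closely.

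**Working it through.** The plan gives no figure to reproduce; the check is one of logic. Let S and D be the falls in SBP and DBP in mmHg. Assume symptoms are present and the heart-rate rise is 35 bpm, so that the heart-rate criterion is met on any reading.

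- Hypotension: S ≥ 20 **or** D ≥ 10.
- POTS, literal reading: S ≥ 20 **and** D ≥ 10.
- POTS, exclusion reading: **not** (S ≥ 20 **and** D ≥ 10).

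**Four illustrative participants**

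| Fall S/D | POTS, literal | POTS, exclusion | Hypotension |
|---|---|---|---|
| 5/2 | no | yes | no |
| 25/5 | no | yes | yes |
| 10/12 | no | yes | yes |
| 25/12 | yes | no | yes |

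The two POTS columns are exact opposites, so the choice of reading reverses the pressure part of POTS for every participant.

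**All whole-number pairs, S from 0 to 40 and D from 0 to 20**

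- Pairs in total: 41 × 21 = 861.
- Both falls present: 21 × 11 = 231.
- Hypotension: 861 − 20 × 10 = 661.
- Literal reading: 231 pairs meet the POTS clause, and all 231 also meet hypotension.
- Exclusion reading: 861 − 231 = 630 pairs meet the POTS clause. Those that also meet hypotension are the pairs with exactly one of the two falls: 661 − 231 = 430.

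These are cells on a grid, not patient frequencies. They show that overlap exists on both readings, not how common it is.

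**Overlap disappears if the clauses are complementary.** If both use *or*, the split is 661 hypotension and 861 − 661 = 200 without. If both use *and*, it is 231 and 630. Overlap is 0 either way.

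**Heart-rate wording**

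- *120 bpm.* A rise of 120 or more is already a rise of 30 or more, so as an increase the second limb adds nothing. As a rate it matters: an illustrative participant going from 95 to 122 bpm has a rise of 27 bpm, which is borderline if 120 is a rise and POTS if it is a rate.
- *Borderline.* Read as a floor of 27, the class also takes in every rise of 30 or more. Read as a range of 27 to 29, it leaves a rise of 29.5 unassigned, which is possible because the inputs are 30-second averages.
- *Sustained.* The text neither says that the 30-second peak is the test of a sustained rise nor supplies another feature for it.

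**The case against.** The strongest reply is that the literal reading contradicts the clause's own opening words. The section lists POTS and hypotension as separate classes and says that classification follows a consensus statement, so the authors very probably meant that a significant fall must be absent. That stands: a reader might infer that the plan *requires* a pressure fall for POTS, so that every POTS case is also hypotensive and none has stable pressure. The documents do not support this as the intended rule; it follows only from the less plausible reading. But the exclusion reading does not remove the overlap. Nor does the citation settle it: the text names a European autonomic federation's statement, while the titles of the two references given are a heart rhythm society statement and a report of a National Institutes of Health meeting. Borderline POTS is expressly a definition for this study.

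A reader might also infer that taking the peak 30-second window inflates the heart-rate rise and so overcounts POTS. The text does not link that peak to *sustained*. Any excess in bpm would rest on an assumed variability, and measuring it against a 10-minute mean uses a benchmark that the protocol does not set. What stands is that *sustained* is undefined.

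The remaining replies are fair on importance. As an increase the 120 bpm limb is redundant, so context points to a rate. Sympathetic skin response and heart rate variability also assess autonomic function. Section 18 calls the characterization comparison exploratory, and Section 20 does not name the tilt classes. If each class were tested as a separate yes/no variable, overlap would not invalidate the chi-square test, but the reading applied would still decide who counts as POTS.

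**Conclusion.** The rules are defective as written. The POTS and borderline-POTS pressure clause and the hypotension rule overlap on either reading, with no precedence to resolve it, so classes can overlap or be misassigned. This rests on the written connectors and thresholds alone and needs no assumption about variability or prevalence.

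The number of participants affected cannot be stated. It depends on how assessors applied the rule and, on the exclusion reading, on how many had both a qualifying heart-rate rise and an isolated systolic or diastolic fall; the documents give neither. It would therefore be too strong to say that the reported classes will be wrong. The consequence is confined to a secondary, exploratory characterization outcome. The primary outcome, change in fatigue VAS at 48 hours, is untouched. The correction should be made, but it does not threaten the trial's main conclusion.

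**What to change.** The sponsor should reconcile the passages; the choice of diagnostic criterion is theirs.

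1. Rewrite the POTS, borderline-POTS and hypotension sentences so that the pressure clauses are complementary, with the same thresholds and connector logic throughout the section.
2. State the order in which the classes, including syncope, are assigned, so that each participant falls in one.
3. Say whether 120 bpm is a rate or a rise. Give borderline POTS one unambiguous interval that leaves no gap below 30 bpm, and either add it to the class list or say where those participants are counted.
4. Tie *sustained* to a stated extracted feature.
5. Re-derive the classes by script for both groups and both time points, and report the rule that was actually applied.

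The cost is low. The section describes continuous recording and beat-to-beat analysis, so no new testing is needed provided that the signals were kept, which is an assumption. The downside is that the POTS count, and any comparison built on it, may change.
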